## Abstract

**Background:**

Holistic health care includes sexuality. For people with mental illness, sexuality is an essential element of recovery. However, sexuality is often overlooked in mental health settings in Japan and elsewhere. Therefore, practitioners need to recognize sexuality as a legitimate area of care and acquire the skills and attitude**s** required to provide appropriate support. To address this gap, we developed a training program for practitioners through coproduction among peers with mental illness, researchers, and practitioners.

**Objective:**

This randomized controlled trial (RCT) in Japan compares an intervention group that participates in the program with a control group that does not and evaluates the program’s effectiveness in improving practitioners’ knowledge, attitudes, and confidence in providing sexuality-related support to clients with mental illnesses.

**Methods:**

The study participants are qualified practitioners aged 18 years or older who provide community-based support to people with mental illness. This 4-hour program combines comprehensive sexuality education with content specific to mental illness and deepens participants’ knowledge and skills through textbooks and case studies. The program is delivered in small groups of up to 8 participants by 2 facilitators: a practitioner and a peer with mental illness. Peer facilitators have experience facilitating sexuality-related group programs. The study design is a 2-arm parallel group RCT. After a baseline assessment, participants will be randomly assigned to an intervention or control group. Participants in the intervention group will complete an online questionnaire at baseline (T1), immediately after the program (T2), and 1 month after the program (T3). Participants in the control group will not receive the program during the study period and will complete the same 3 assessments (T1 to T3). Outcomes focus on participant competence rather than client condition. The primary outcome is confidence in providing sexuality-related support, measured using the self-assessment scale (lack of quality for sexuality education). Secondary outcomes include attitudes regarding sexuality (Attitudes Toward Sexuality Scale), knowledge of sexuality education, and knowledge of preconception care for people with mental illness. The target sample size is 76.

**Results:**

Funding was awarded in April 2023. Recruitment began in June 2025, and as of March 12, 2026, 57 participants had enrolled, 46 of whom had completed the final assessment. Analysis has not yet been conducted, and final data collection is anticipated by December 2026.

**Conclusions:**

To our knowledge, this will be the first RCT on a sexuality support training program for mental health practitioners. If effective, the program may help practitioners provide better support to people with mental illness and, in the long term, contribute to their recovery.

## Introduction

### Background

When health care practitioners provide care, they emphasize a holistic approach [1], and sexuality is an integral part of that care [2]. The World Health Organization (WHO) [3] defines sexuality as “a central aspect of being human throughout life is sexuality, which encompasses sex, gender identities and roles, sexual orientation, eroticism, pleasure, intimacy, and reproduction.” Literature reviews have revealed that health care practitioners receive limited education on sexuality and would benefit from additional training [4,5].

The guidelines for comprehensive sexuality education, issued by the United Nations Educational, Scientific and Cultural Organization (UNESCO) in its *International Technical Guidance on Sexuality Education: An Evidence-Informed Approach* [6,7], have become the global standard. Comprehensive sexuality education has been implemented in many countries, primarily for adolescents [8-10].

In Japan, sexuality has long been a taboo topic [11]. After the first patient with AIDS was identified in 1985, an AIDS panic ensued, and sexuality education became widespread [12]. In 2002, a politician claimed that sexuality education was encouraging sexual activity, and sexuality education then declined sharply [12]. Sexuality education has lagged behind international standards for many years [13,14]. Only recently have school teachers worked on comprehensive sexuality education, including the development of teaching materials that reflect both the guidelines and the local cultural and social context [15]. Regarding sexual minorities, homosexuality has historically been regarded as an abnormal sexual desire. However, the term LGBT (lesbian, gay, bisexual, transgender/transsexual) has been widely used since the early 2010s, and public awareness has increased [16]. Nevertheless, a nationwide survey revealed that 11.3% of the general population did not understand the meanings of the questions about sexual minorities [17], indicating that understanding remains insufficient. Furthermore, 14% of people reported having negative feelings toward homosexual colleagues [17], indicating that acceptance of sexual minorities is still limited. Thus, in Japan, sexuality has been considered taboo and has not been adequately taught, and prejudice against sexual minorities still persists, leading to resistance to discussing sexuality [18].

Illness can affect sexuality, including in the context of mental illnesses [19,20]. Mental illness is a global public health challenge with a lifetime prevalence of 12% to 47.4% [21], with approximately half of individuals developing the illness by the age of 14 years [22]. Review studies on sexuality among people with various mental illnesses have shown high rates of unintended pregnancy, domestic violence, sexual dysfunction due to medication side effects, and divorce [19,23,24]. Furthermore, despite being sexually active, people with mental illness may experience psychological suffering, including sexual stigma, low sexual confidence, and unmet sexual desires [19,20,25,26].

However, sexuality is still largely ignored in mental health settings [27]. Mental health practitioners may avoid the topic because they see it as outside their scope of practice, give it low priority, or feel uncomfortable discussing it; similar barriers have been reported among health care practitioners more broadly [28,29]. Additional barriers in mental health care include concerns about worsening a client’s mental health condition and the view that sexuality is not part of recovery [30-33]. Recovery is now a central concept in mental health services and a key goal of rehabilitation [34], and romantic loneliness is associated with poor recovery [35]. Intimate relationships may therefore form part of recovery, and sexuality may be an important barrier to address [20]. In this study, sexuality is defined as an important part of building intimate relationships and as an essential element of recovery for people with mental illness.

For people with mental illness, 1 major problem is that practitioners rarely address sexuality [27]. In a survey of people with mental illness in Japan, 59% reported having no one to consult about sexuality, and among those who did, most turned to psychiatrists, friends, or family members, whereas only a few consulted psychologists, nurses, or social workers [36]. Health care practitioners often lack sufficient knowledge and appropriate attitudes regarding sexuality [18]. Mental health practitioners, therefore, need the knowledge, attitudes, and confidence required to provide counseling and comprehensive sexuality education as part of recovery-oriented care for people with mental illness.

Previous international studies have examined these barriers to addressing sexuality in mental health care [37]. These studies suggest that mental health practitioners lack knowledge and skills related to sexuality support [31] and require training to overcome these barriers [30]. However, there are few studies on the development of training about sexuality for people with mental illness, with only a small number of interventions focusing on training for mental health nurses [38,39], mainly for hospitalized patients rather than clients living in the community. Psychiatric hospitals are settings focused on crisis management, where sexuality support is reported to be less of a priority [40]. A systematic review also reports implicit norms that view inpatient sexual behavior as risky [41]. Institutions pose special challenges with patient sexuality, including physical space [27]. For these reasons, sexuality support in inpatient settings may differ substantially from sexuality support in community settings.

In Japan, policies have shifted from inpatient treatment to community care, and mental health practitioners increasingly support people with mental illness in community settings [42]. Community-based mental health practitioners include a wide range of professionals, such as nurses, social workers, occupational therapists, and others [43]. Because support related to sexuality is especially relevant to community settings [44], it is important that these practitioners are able to provide effective support. To our knowledge, however, no training program in Japan has been reported for mental health practitioners who support the sexuality of people with mental illness.

Against this background, we developed a support training program (RIKASEKU-SAPOPRO) through coproduction among peers with mental illness, researchers, and mental health practitioners. The program was based on the *International Technical Guidance on Sexuality Education: An Evidence-Informed Approach* [7] and was designed to enable mental health practitioners to support the sexuality of people with mental illness living in the community. The outcome variables—knowledge, attitudes, and confidence in providing sexuality-related support—were selected based on an intervention study of a sexuality support training program for hospital mental health nurses [39]. This study uses a randomized controlled trial (RCT) to compare an intervention group that participates in the program with a control group that does not.

### Objectives

This study evaluates the effectiveness of a sexuality support training program by examining whether practitioners gain knowledge, improve attitudes, and build confidence in providing sexuality-related support to their clients with mental illnesses.

## Methods

### Study Design

The study design is an RCT with a 2-arm parallel group comparison. Participants are randomly assigned to either the intervention or control group after the baseline assessment. Participants in the intervention group complete an online questionnaire at 3 points in time: baseline (T1), immediately after the program (T2), and 1 month after the program (T3). The control group receives no program during the study period and is also assessed 3 times (T1-T3). To ensure that all participants are given an opportunity to take part in the program, the control group is offered the program after the final assessment (T3) has been completed. This protocol was developed and is reported in accordance with the Standard Protocol Items: Recommendations for Interventional Trials (SPIRIT) 2013 checklist (Checklist 1).

### Study Setting

This study was conducted in Japan. Participants were recruited through a dedicated research website and through information distributed to community-based institutions and networks that support people with mental illness.

### Study Participants

The study participants are qualified practitioners aged 18 years or older who provide community-based support to people with mental illness. There are no restrictions on profession; eligible practitioners include physicians, nurses, social workers, psychologists, occupational therapists, and others. The certifying body of professional qualifications, such as a national or municipal authority, is not used as an eligibility criterion. Since the 21st century, Japan has experienced increased immigration, including labor immigration [45]. For this reason, no restrictions are placed on ethnicity, and ethnicity is collected as a demographic characteristic. The exclusion criteria are the inability to participate in the online survey or Zoom video conferencing and difficulty participating in group discussions in Japanese.

### Intervention Program

#### Program Coproduction Process

RIKASEKU-SAPOPRO is a sexuality support training program aimed at recovery. Although mental health services have traditionally been developed by researchers and health practitioners, the concept of coproduction with service users has recently been identified as central to the provision of effective recovery-oriented services [34]. This program has been developed through coproduction among 5 peers with mental illness (out of these 5 peers, 2 of them were qualified social workers) and 7 researchers and/or practitioners (4 nurses, 1 psychiatrist, 1 obstetrician-gynecologist, and 1 social worker). Among them, 2 are experts in sexuality education, and 1 is involved in awareness-raising activities as a sexual minority. We have already cocreated a program about intimate and romantic relationships with peers with mental illness [46], in which we worked with about 25 peer facilitators. We recruited peers who were interested in this research project to establish a research team and develop the current program.

From the initial idea of program development to program design, selection of evaluation criteria, and implementation, researchers, practitioners, and peers were equally involved, and all opinions were respected. To support equal participation, we adopted a nonhierarchical form of address and held social gatherings to build trust. The research team worked together for 2 years before the intervention started. During this period, a questionnaire survey of 300 people with mental illnesses [36], interview studies with 23 women with mental illness [47], and interviews with 26 practitioners were conducted, and the findings were reflected in the program textbook. All aspects, including the program’s structure, textbook materials, the style of facilitation in peer-practitioner pairings, and the defined outcome variables, underwent discussion and were finalized by this team. A total of 3 pilot programs were conducted and reviewed.

#### Program Overview and Development Process

Table 1 provides an overview of the program. The 4-hour program combines comprehensive sexuality education with content specific to mental illness, deepens knowledge through textbooks, and develops support skills through case studies. The program is conducted in small groups of up to 8 participants, with 2 facilitators: a health care practitioner and a peer with mental illness. The entire program is based on the *International Technical Guidance on Sexuality Education: An Evidence-Informed Approach* [7]. We use the sexuality education textbook “Mana Book” (level 4), which is based on the *International Technical Guidance on Sexuality Education: An Evidence-Informed Approach* and was first developed in Japan for individuals aged 15 to 18 years.

**Table 1. T1:** Components of the RIKASEKU-SAPOPRO program^a^.

Modules and time duration (min)		Lesson	Purposes	Contents
Module 1—introduction key concepts: (1) “Relationships” and (2) “Values, Rights, Culture, and Sexuality”				
7		Introduction	Creating a safe place	Program overview and review of ground rules
8		Self-introduction	Getting to know each other and feeling safe	Description of usual work, motivation for participation, and icebreaker
10		Relationships and values	Gaining knowledge and awareness	Family structure, interpersonal boundaries, and reactions to sexuality
10		Sexuality support	Gaining awareness	Skills for counseling and responding to questions about the characteristics of sexual topics, the background and nature of worries, and values
20		Case studies (2 cases)	Acquiring support skills	A case where the client believes they are in love and a case where a woman is being sexually exploited but is unaware.
5		Reflection	Summarize own thoughts	Participants share their awareness and impressions.
Module 2—key concepts: (3) “Understanding gender,” (6) “The human body and development,” and (7) “Sexuality and sexual behavior”				
10		Sexual diversity	Gaining knowledge and awareness	SOGIE^b^
10		Gender roles, sexual dysfunction, and sexual pleasure	Gaining knowledge and awareness	Gender-based attitudes, sexual dysfunction, sexual response, and sexual pleasure in people with mental illness
25		Case studies (2 cases)	Acquiring support skills	A case of a person who has discovered they are a sexual minority and a case of unfulfilled sexual desires
5		Reflection	Summarize own thoughts	Participants share their awareness and impressions.
Module 3—key concepts: 5 “Skills for health and well-being”; 4 “Violence and staying safe”				
10		Sexual independence and sexual consent	Gaining knowledge and awareness	What is sexual autonomy and consent, and how does the media influence it?
10		Sexual violence and sexual crimes	Gaining knowledge and awareness	Survivors of domestic violence and sexual crimes among people with mental illnesses; criminal law reform regarding sexual violence and sexual crimes.
25		Case studies (2 cases)	Acquiring support skills	A case where sexual consent was mistakenly obtained, and a case of economic exploitation using romantic feelings
5		Reflection	Summarize own thoughts	Participants share their insights and impressions.
Module 4—key concept: (8) “Sexual and reproductive health”				
7		Preconception care and pregnancy	Gaining knowledge and awareness	Preconception care for people with mental illnesses, pregnancy, and contraception
13		Whether to have a child and pregnancy	Gaining knowledge and awareness	Examples of people with mental illness worrying about whether to have children, pregnancy anxiety, unexpected pregnancies, and sexually transmitted diseases
13		Case study (1 case)	Acquiring support skills	The case of a woman suffering from mental illness and anxiety about raising her children
10		How to consult	Gaining knowledge and awareness	Skills to receive SOS calls and provide counseling for people with mental illnesses
7		Overall comments	Program completion	Participants share their overall thoughts on the program.

a Structure: combination of comprehensive sex education and content specific to mental illness, designed to deepen knowledge and support skills through textbooks and case studies. The program is conducted in small groups of 8 people or fewer, led by a practitioner and a peer, and spans 4 hours.

b SOGIE: sexual orientation, gender identity, and gender expression.

In addition, an original textbook was developed to address concerns specific to mental illness. All modules include a textbook section for knowledge confirmation and a scenario-based case study section, which is a major strength of this training format [4]. After confirming their knowledge through the textbook, participants share their impressions and gain new insights by listening to the opinions of others. During discussions of the case studies, participants exchange opinions on the types of support that can be provided for each case.

#### Program Facilitators

The program is facilitated by pairing a peer with mental illness and a practitioner. In this study, peer facilitators are expected to provide participants with perspectives that differ from those of practitioners because they are experts based on their own lived experience. In Japan, there are no formal qualifications for peer supporters, and no training is required to act as a peer supporter. To recruit experienced peers for this program, we selected individuals from among peer facilitators in an intimate relationship group program [46,48]. Practitioner facilitators were initially recruited from among those who had cooperated with interviews about sexuality in order to identify individuals who were interested in the topic. Subsequently, we recruited practitioners who had completed the final assessment of the study by asking whether they wished to serve as facilitators. All practitioner facilitators hold national qualifications, such as social worker or nurse. All facilitators received 6 hours of training for this program. As of March 12, 2026, 10 peer facilitators and 14 practitioner facilitators had completed the training. A facilitator manual was created to promote adherence to the intervention protocol by specifying in detail the sections of text to be read and the time allotted for each discussion. [name] observes all the intervention sessions to ensure that they are implemented according to the manual.

### Random Allocation and Blinding

KN prepared an allocation list stratified by assigned sex at birth (female or male). In Japan, policy guidance has generally favored assigning practitioners of the same sex for care that service users may perceive as sensitive or embarrassing, partly to protect the rights and dignity of people with disabilities [49]. Practitioner sex may therefore influence the effectiveness of the program, as providing sexuality-related support to same-sex versus opposite-sex clients may affect the content and type of counseling offered. In addition, understanding of sexual diversity remains limited in some settings in Japan; even health care practitioners may encounter discrimination related to sexual minority status [36], and some individuals may be reluctant to disclose their gender identity even when distressed [50]. These sociocultural factors influenced the study design and informed the decision to avoid stratification based on gender identity. Randomization was therefore stratified by sex assigned at birth in order to reduce the privacy burden associated with collecting sensitive personal information.

The allocation is performed using REDCap (Research Electronic Data Capture; Vanderbilt University), a widely used web application for building and managing online surveys and databases. KN prepared the allocation list before enrollment began. REDCap locks the randomization model to ensure that it is not modified once a study becomes active. After [name] confirms that participants have responded to the online survey (T1), [name] enters the assigned sex at birth data into REDCap, and random allocation is performed automatically. [name] communicates the allocation results displayed in REDCap to participants by email. Group assignment is unknown to researchers other than [name]. [name] is the sole individual with access to the test dataset, which is managed through REDCap. [name] is responsible for extracting group information from the final dataset and subsequently providing the dataset to [name] for statistical analysis.

### Sample Size

We plan to recruit 76 participants. A previous study [51] conducted a similar intervention; in that study, the average scale score of the primary outcome variable before the training was 23.39, and the average scores 1 week and 3 months later were both 18.56. In our study, we assume that the intervention group’s average score 1 month after the intervention will be 18.56, compared with 23.39 for the control group. Furthermore, the previous study [51] that examined the validity of the scale reported an average of 19.5 (SD 5.5). In our study, taking into account the intervention and the characteristics of the participants, the SD is assumed to be 6.5.

Under the above assumptions, if a 2-tailed *t* test is used with an α error of 5% on both sides and a power of 80%, the required sample size is 60 (n=30 for each group). After considering a dropout rate of 20%, the required sample size is 76. The study’s intervention is administered on a group-by-group basis; however, given the nature of the intervention, the expected small group effect allows for a sample size calculation method that presumes independence.

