### Analysis Plan

#### Statistical Analysis

The primary analysis will be conducted on the full analysis set (FAS), with supplementary analyses performed using the per-protocol set. The FAS will include all enrolled participants except those who meet the following exclusion criteria: (1) no response at T1 and (2) not randomized. The per-protocol set will consist of participants in the FAS except those who meet the following exclusion criteria: (1) no response at T2 and/or T3, (2) assignment to the intervention group but attendance at fewer than half of the program sessions, and (3) withdrawal from the study during the intervention period.

Baseline data for continuous variables will be summarized as mean and SD or as median and IQR, whereas categorical variables will be summarized as frequencies and percentages.

For the main hypothesis 1, a Student 2-tailed *t* test will be conducted, and a 95% CI will be calculated. An analysis of covariance will be conducted with assigned sex at birth and baseline values included as covariates, and the difference in least squares means, along with its 95% CI, will be estimated.

For hypotheses 2 and 4, a mixed-effects model for repeated measures (MMRM) will be conducted with group, time points (T1, T2, and T3), and the interaction between group and time points as fixed effects, and participants as a random effect. The variance-covariance structure of the error terms in the MMRM will be tested in the following order: unstructured, compound symmetry, and auto-regression. The estimation results based on the first successful convergence of the specified structure will be adopted. MMRM estimation will be conducted using the restricted maximum likelihood method.

For hypothesis 3, the same analysis as that for the main hypothesis will be conducted.

For hypotheses 5 and 6, the Wilcoxon rank-sum test will be conducted at time points T2 and T3. Since these are secondary end points, no adjustments for multiplicity will be made.

All statistical analyses will be conducted using IBM SPSS (Statistical Package for the Social Sciences) Statistics (version 23).

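### Training groups exist in the intervention arm only, but every planned test treats participants as independent; any positive within-group correlation makes the intervals too narrow and lifts the 5% error rate

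*Protocol article*

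**What the plan says.** - **Delivery.** Program Overview and Development Process: "The program is conducted in small groups of up to 8 participants, with 2 facilitators: a health care practitioner and a peer with mental illness". Under Study Design, controls receive no program until their final assessment is complete, so grouping arises in one arm only.
- **Facilitators.** Program Facilitators reports that "10 peer facilitators and 14 practitioner facilitators had completed the training" by 12 March 2026. It also describes a manual, six hours of training and observation of every session.
- **Sample size.** "We plan to recruit 76 participants", on the assumption that "the intervention group’s average score 1 month after the intervention will be 18.56, compared with 23.39 for the control group" and that "the SD is assumed to be 6.5". This gives 30 per arm, or 76 in total after 20% dropout. The section acknowledges group delivery, then concludes that "the expected small group effect allows for a sample size calculation method that presumes independence". No ICC, design effect or source is given.
- **Analysis.** Statistical Analysis: "For the main hypothesis 1, a Student 2-tailed *t* test will be conducted, and a 95% CI will be calculated". The ANCOVA adjusts for sex at birth and baseline. The MMRM has the participant as its only random effect. The two knowledge outcomes use the Wilcoxon rank-sum test. None of these contains the training group.

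**The concern.** People trained in the same session share facilitators, discussion and one another's views, so their later scores may resemble each other more than scores from different sessions. By the durations in Table 1, case studies (20 + 25 + 25 + 13 = 83 minutes), reflections (15) and closing comments (7) make up 105 of 210 listed minutes. Half the program is therefore group exchange, and the primary scale's items (knowing how to raise the subject, embarrassment) are close to what is discussed.

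Positive correlation of this kind enlarges the variance of the intervention mean and leaves the control mean alone. A test that ignores it uses too small a standard error. That would affect the primary comparison and every secondary comparison between arms. The article's one justification concerns the sample size calculation. It is unquantified, and it is silently carried over to the analysis.

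**Working it through.** **Inputs.** From Sample Size: means 18.56 and 23.39, SD 6.5, two-sided 5%, 80% power, 30 per arm, 76 after 20% dropout. From Program Overview: at most 8 per group. From Results: no dropout among 57 enrolled. Assumed, because the article gives no values: ICC 0.01 to 0.10, group size m of 4 to 8 and, where stated, a baseline–outcome correlation of 0.5.

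**1. The plan's own figure.** Difference 23.39 − 18.56 = 4.83; 4.83/6.5 = 0.743 SD. The exact noncentral t gives 79.4% power at 29 per arm and 80.8% at 30, so 30 per arm is right under independence. 30/0.8 = 37.5, rounded up to 38 per arm, or 76. At 38 per arm the same test has 89.2% power.

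**2. Standard error with one clustered arm.** Design effect DE = 1 + (m − 1)·ICC.
- True SE = SD·√(DE/n + 1/n); planned SE = SD·√(2/n); ratio = √((1 + DE)/2).
- Example, m = 8 and ICC 0.05: DE = 1 + 7 × 0.05 = 1.35; ratio = √(2.35/2) = 1.084.

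**3. True error of the planned 5% t test.** Large-sample form: 2·[1 − Φ(1.96/ratio)]. In the example 1.96/1.084 = 1.808, giving 7.1%. The last column is simulation at 30 per arm.

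| ICC | DE, m = 4 / 8 | SE ratio, m = 4 / 8 | Error by formula, m = 4 / 8 | Simulated, m = 4 to 8 |
|---|---|---|---|---|
| 0.01 | 1.03 / 1.07 | 1.007 / 1.017 | 5.2% / 5.4% | – |
| 0.02 | 1.06 / 1.14 | 1.015 / 1.034 | 5.3% / 5.8% | 5.4–5.9% |
| 0.05 | 1.15 / 1.35 | 1.037 / 1.084 | 5.9% / 7.1% | 5.8–6.8% |
| 0.10 | 1.30 / 1.70 | 1.072 / 1.162 | 6.8% / 9.2% | 6.6–8.9% |

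The two agree within a few tenths of a point. The gaps reflect simulation error and the fact that 30 does not divide evenly into groups of 4 or 8.

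**4. Rejection rate of the planned t test when the assumed effect is real.** Simulated at 30 per arm it stays at about 78–80% for ICC up to 0.10, against 80.8% under independence.

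**5. Power of a cluster-adjusted analysis.** Satterthwaite df = (DE + 1)² / [DE²/(k − 1) + 1/(n − 1)], with k = n/m groups.
- Example, n = 30, m = 8, ICC 0.05: SE = 6.5·√(2.35/30) = 1.819; 4.83/1.819 = 2.655.
- k = 3.75; df = 5.5225/(1.8225/2.75 + 1/29) = 7.9; critical value 2.31; power 64%.
- Baseline adjustment at r = 0.5 reduces the SD to 6.5·√0.75 = 5.63.

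| ICC 0.05 | m = 4 | m = 6 | m = 8 |
|---|---|---|---|
| 30 per arm, no baseline | 75% | 70% | 64% |
| 38 per arm, no baseline | 85% | 82% | 78% |
| 30 per arm, baseline r = 0.5 | 86% | 82% | 77% |
| 38 per arm, baseline r = 0.5 | 93% | 91% | 88% |

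Part of the fall at 30 per arm comes from having few groups rather than from the ICC. With m = 8 and ICC 0 the same formula already gives 74%. Conversely, by the normal approximation, which makes no df allowance, the wider SE alone takes power from 82.1% to 75.6% at ICC 0.05.

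**The case against.** The strongest reply is that the authors considered the matter and had grounds to expect a small effect. The program is a single four-hour event, the manual scripts the reading and timing, every session is observed, the books are read individually beforehand, and the outcome is self-rated a month later. Eight is a ceiling. With 57 enrolled in roughly nine months, even accrual and 1:1 allocation imply about three intervention participants a month. Since they must attend within two months of allocation, groups of about six or fewer are likely. This stands as a reason to expect the lower part of the range. It does not remove the shared discussion that fills half the timetable, and it does not supply a number.

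Four stronger readings are tempting and are not supported:
- **That the intervals are certainly too narrow.** This needs an ICC above zero, which the article does not report; at 0.01 the distortion is slight.
- **That the trial is underpowered.** The planned t test barely loses power. The shortfall belongs to a cluster-adjusted analysis at 30 per arm. It is largely recovered at 38 per arm, where no one had dropped out by March 2026, and with the planned baseline adjustment. More participants would not, however, correct the error rate.
- **That facilitators are shared across groups.** The article counts trained facilitators but does not say that any of them leads more than one group.
- **That a full two-arm design effect applies.** Controls are ungrouped, so it would exaggerate the problem.

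The statistical analysis plan is not shown and may contain a clustering sensitivity analysis. If so, only the sample size sentence needs attention. The article, however, spells out covariates, random effects and covariance structures, and asserts independence for the sample size, so this is a stated choice rather than a detail left out.

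**Conclusion.** The concern holds as a conditional statement about standard errors and false positives, and should be fixed. The article's sample size arithmetic is correct under independence. Independence itself rests on an unquantified assertion, made for the sample size only, while all four planned methods depend on it. With an assumed ICC of 0.02 to 0.10 and groups of 4 to 8, the nominal 5% primary t test runs at about 5.4% to 8.9%, and its standard error is too small by a factor of about 1.02 to 1.16. These sizes rest entirely on the assumed ICC and group sizes. Low power is not the main problem and should not be presented as one.

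**What to change.** 1. Record the training-group identifier for each intervention participant, if this is not already done.
2. Before analysis, pre-specify a partially nested version of the baseline- and sex-adjusted primary model, the hypothesis 3 ANCOVA and the MMRM: a random training-group effect in the intervention arm only, small-sample df, and a stated fallback if that variance is estimated at zero. Report it beside the independence analysis, with the estimated ICC.
3. For hypotheses 5 and 6, a random effect cannot be added to the Wilcoxon test. Name a cluster-aware alternative, or state the limitation.
4. Replace the independence sentence in Sample Size with power over a stated ICC range (for example 0.02 to 0.10) at 30 and 38 per arm.

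**Cost.** Slightly wider intervals, fewer degrees of freedom, an imprecise ICC estimate from few groups, and a less favourable stated power. No extra participants and no change to the program. Analysis has not begun and data collection runs to December 2026, so all of this can still be pre-specified; added after results are seen, it would be post hoc.
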